#### Community advisory board (CAB) and staff exchange programmes (SEPs)

We will conduct FGDs to assess CAB experiences and perspectives of community acceptability of PrEP for AGYW. A SEP using observations and staff IDIs will allow those doing the same work at different sites to recognize and discuss implementation differences that may inform optimized service delivery and participant engagement. FGDs and SEPs will assess community and study impact on adherence or attendance, as well as determining additional differences in community and organization that may influence these study outcomes.

#### Data management and quality assurance

Data will be stored in a secure, password-protected, web-based database which will only be accessible to authorized project staff. Tablet computers used for ACASI interviews will be password protected and will be stored securely at the Foundation for Professional Development (FPD) offices in the study districts. Paper records of participants will be kept in lockable filing cabinets at FPD offices. Paper records, excluding informed consent forms, will only contain PINs. A separate, access-controlled, link log database will be developed and maintained by the data manager. Qualitative data including audio files and password-protected transcripts will be stored on a secure, access-controlled cloud-based database (SharePoint). Double-data entry of laboratory results will be employed when capturing participant data onto RedCap. Automated data quality checks and skip patterns will be built into RedCap and ACASI. Research assistants will conduct onsite data quality checks daily. Scheduled and unscheduled data quality inspections will be carried out by the data quality assurance personnel in order to ensure high data quality standards. The principal investigators, or their designate, will randomly select 10% of all participant files for inspection every 3 months.

#### Study oversite, data safety and monitoring board (DSMB), and study auditing

The co-principal investigators/corresponding authors take responsibility for the scientific validity of the study protocol, assessment of study quality and conduct, as well as for the scientific quality of the final study report. The primary author oversees the coordinating centre and takes responsibility for the day-to-day study implementation in collaboration with three other co-authors (Foundation for Professional Development). A DSMB will be made up of four invited national and international experts, at least two of whom are clinically trained and knowledgeable about PrEP and at least one biostatistician. DSMB members will have no direct association with this study and will be independent from any professional or financial conflict of interest with the research project and/or study investigators. The DSMB will review in aggregate on a bi-annual basis, any adverse events (AEs) that occur. Though no serious adverse events (SAEs) are reasonably expected during this trial, should they occur the DSMB will review them in real time. Trial conduct will be continuously audited as part of quarterly meetings of the study team, and annually by the University of Cape Town Human Research Ethics Committee as part of mandatory renewal of ethics approval.

### Laboratory testing, STI treatment, and clinical follow-up

#### HIV rapid testing

HIV counselling and testing will be performed every 3 months, per South African national guidelines [50] (Table 2). Those with a positive confirmatory test will have venous blood drawn to test for HIV drug resistance. Furthermore, those testing positive for HIV will be terminated from the study and provided a referral letter for HIV care and treatment.

#### STI testing and treatment

We will test for *Chlamydia trachomatis* (CT), *Neisseria gonorrhoeae* (NG), and *Trichomonas vaginalis* (TV) using a self-collected vaginal swab at baseline and again at months 6, 12, and 24. Self-collected swabs will be shipped monthly to the National Institute for Communicable Diseases (NICD; Johannesburg, South Africa) for nucleic acid amplification testing (NAAT) using the Aptima Combo 2® Assay (Hologic, San Diego, USA) for *Neisseria gonorrhoeae* and *Chlamydia trachomatis* and using the Aptima® Trichomonas vaginalis Assay (Hologic, San Diego, USA) for *Trichomonas vaginalis.* Negative test results will be notified at the next study visit. Positive test results will be notified immediately upon result availability via site-based visits or phone calls. Those with a positive STI test result will be provided a copy of their results and a treatment referral letter per South African STI guidelines [58].

Syphilis testing will be conducted during the enrolment visit only, using the Alere Determine™ Syphilis TP rapid test. Negative tests will be reported by the study nurse to participants; patients testing positive will be referred for further laboratory confirmatory testing and treatment as indicated. All enrolled participants will be tested for Hepatitis B antigen (HBsAg), performed by the National Health Laboratory Service. Participants with a negative test result will be provided hepatitis B vaccination per the South African vaccination schedule [59]; those that test positive will be asked to provide blood for ALT and AST testing to determine liver function and referred for care and treatment. Neither the syphilis nor hepatitis B test results will impact study eligibility.

#### Pregnancy testing

Urine-based pregnancy testing to detect human chorionic gonadotropin will be conducted every 3 months. If a participant becomes pregnant while enrolled in the study, they will be provided referral letters for prenatal support and care, and counselled on taking PrEP while pregnant, and will be allowed to decide whether they want to continue PrEP. Participants who continue taking PrEP will be monitored by the study clinician and nurses, with pregnancy milestone and birth outcomes recorded and monitored.

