##### Referral for PrEP services and study enrolment

Eligible participants interested in PrEP will be provided a copy of their HIV test results and a referral letter for PrEP initiation at our study sites, which will be co-located with pop-up testing sites A and B. Upon presenting to a PrEP study site, participants will be consented, asked to provide contact details, tested for syphilis and pregnancy, and asked to submit a self-collected vaginal swab for further STI testing (Table 2). If pregnant, participants will be provided a referral letter for antenatal care services in lieu of PrEP initiation, as South Africa has not yet approved PrEP initiation during pregnancy. Prior to departure, participants will receive their syphilis test results, with a treatment referral if applicable.

Participants will be asked to provide a blood sample for hepatitis B testing and creatinine clearance, randomized, and then provided a 30-day supply (1 bottle) of DIDIVIR (CIPLA generic for Emtricitabine 200 mg/ Tenofovir Disoproxil Fumarate 300 mg); those randomized to an intervention group will be reminded of their first adherence session date. All participants will be asked to return for an orientation visit 2 weeks post-enrolment to meet with their adherence counsellor, and a study nurse to review any test results, assess side effects and acute HIV symptoms, and receive the first of three hepatitis B injections if indicated.

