### Ethical considerations and trial registration

PrEP has been approved for use by international and domestic governing bodies in South Africa. Written informed consent will be obtained from participants at multiple time points, including prior to baseline questionnaire, PrEP initiation, and any qualitative interviews. The study protocol has received full ethical approval from the University of Cape Town Human Research Ethics Committee (Ref: 289/2018) and has been registered with ClinicalTrials.gov (NCT03977181). Any and all protocol modifications and annual ethics renewal will be submitted to the University of Cape Town Human Research Ethics Committee for approval.

There are no anticipated problems that are detrimental to the participants; however, expected clinical side effects of DIDIVIR include nausea, dizziness, and diarrhoea; study nurses will be trained on the Southern African HIV Clinicians Guidelines for PrEP used to identify and manage side effects [62]. All research staff will be trained to identify, probe for, and report AEs and social harms (SHs). Occurrence of AEs and SHs will be collected at every visit and recorded in REDCap. All AEs and SHs, with detailed study notes, will be internally reviewed by the study team. An AE list will be compiled and reviewed by the study DSMB and reported to University of Cape Town IRB. A study clinician will review all abnormal test results, liaise with local clinic doctors, and has the authority to terminate participants based on clinical opinion. Upon completion of their 2-year follow-up, all participants will be provided a referral to their local clinics for continuation of PrEP services.

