### Trial status

This trial was retrospectively registered with ClinicalTrials.gov (NCT03977181) on June 6, 2019. Participant recruitment was initiated on October 22, 2018, with enrolment completion on November 15, 2019. Participant follow-up will continue through November 2022. Protocol version 1.5, 22 May 2019.

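### Pregnancy and birth outcomes are stated to be recorded only for women who continue PrEP after a positive test, so any summary would be selected on a choice made after exposure

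*Protocol article*

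**What the plan says.** All references are to the protocol article.

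- **Who is recorded.** The Pregnancy testing section leaves the decision about drug to the participant, who "will be allowed to decide whether they want to continue PrEP". It then sets the recording rule: "Participants who continue taking PrEP will be monitored by the study clinician and nurses, with pregnancy milestone and birth outcomes recorded and monitored". For a pregnant participant who stops, it mentions referral and counselling and says nothing about recording the outcome.
- **When pregnancy is detected.** "Urine-based pregnancy testing to detect human chorionic gonadotropin will be conducted every 3 months". Table 2 agrees: baseline, then months 3, 6, 9 and so on to 24. Medication is dispensed monthly (the list of monthly activities below Table 2).
- **Which pregnancies are at issue.** At enrolment, "If pregnant, participants will be provided a referral letter for antenatal care services in lieu of PrEP initiation". The exposed pregnancies are therefore those conceived on study.
- **How long women are followed.** The section on ethical considerations gives each woman 2 years: "Upon completion of their 2-year follow-up, all participants will be provided a referral to their local clinics for continuation of PrEP services". The introduction to data collection also refers to a 2-year period, and Table 2 ends at month 24. Trial status says "Participant recruitment was initiated on October 22, 2018, with enrolment completion on November 15, 2019", and then "Participant follow-up will continue through November 2022".

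**The concern.** The article does more than leave a detail unstated. It gives a rule for recording birth outcomes and makes it depend on what the woman decides after a positive test, when exposure has already happened. A woman who stops on learning that she is pregnant has an exposed pregnancy, but no recording of its outcome is stated.

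Followed as written, the rule gives a series made up only of women who chose to continue. Women who stop may differ from them in gestational age at detection, in health or in early complications. The series could not describe outcomes after early exposure followed by stopping, and the DSMB would have birth outcomes for only part of the exposed pregnancies.

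A second question is how long a pregnancy is followed. The 2-year individual follow-up and the November 2022 end date lead to different answers for women still pregnant at month 24, and the article does not say which applies.

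**Working it through.** The article gives no pregnancy figure to reproduce. The check is a reading of the rule plus date arithmetic.

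**1. Exposure before detection.** A woman who conceives just after a negative test is next tested about 3 months later and can collect drug monthly in between. Possible exposure before scheduled detection is therefore up to about 3 months. It is less if she learns of the pregnancy by other means or is not taking the tablets.

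**2. What selection does.** Let *p* be the share of exposed pregnancies in which the woman stops, and *r_c* and *r_s* the rates of some outcome in those who continue and those who stop.

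- All exposed pregnancies: *r* = (1 − *p*)·*r_c* + *p*·*r_s*
- Under the stated rule, only *r_c* is observed
- Difference: *r_c* − *r* = *p*·(*r_c* − *r_s*)

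The documents give neither *p* nor *r_s*, so the size is unknown. It is zero only if nobody stops or if the two groups have the same rate.

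**3. What other data collection supplies for women who stop.**

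- Adverse events are collected at every visit (section on ethical considerations), and stopping PrEP is not stated to end follow-up. Some losses or complications could appear there. Normal births would not, so there is no complete set of outcomes.
- Pregnancies are listed among the interim results shared with stakeholders (Dissemination plans). This gives a count of pregnancies, not their outcomes.

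**4. If individual follow-up ends at month 24.** Time to term is an assumption: 266 days from conception, or about 9 months in round figures.

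- With 266 days: 266 / 30.4375 = 8.7 months, and 24 − 8.7 = 15.3. Conceptions after about month 15.3 reach term after month 24. With conceptions uniform over 24 months and no attrition, the share is 266 / 730.5 = 36.4%.
- With 9 months: 24 − 9 = 15, and the share is 9 / 24 = 37.5%.

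**5. If follow-up runs to November 2022.**

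- Last enrolment 15 November 2019 + 24 months = 15 November 2021.
- A conception on that date + 266 days = about 8 August 2022, before November 2022.

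Under this reading the calendar allows even the latest on-study conception to reach term. The article does not say what is collected between month 24 and that date.

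**6. A pregnancy first found at month 24.** Table 2 schedules a pregnancy test at month 24 but no PrEP pick-up, and continuing women are then referred to local clinics. The study cannot readily apply a rule based on continuing PrEP to such a pregnancy.

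**The case against.** The strongest case against has five parts.

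- **Silence is not exclusion.** No sentence says that outcomes of women who stop will go unrecorded, and a full protocol exists that may cover them. This stands as a caution. It does not remove the point, because the article states the rule and names only those who continue.
- **Other data collection helps.** Adverse events are collected from all participants at every visit, the adverse-event list goes to the DSMB, and pregnancies are counted. This stands in part: some adverse outcomes in women who stop may be captured, but normal births are not.
- **Pregnancy safety is not an aim or an outcome of this trial.** This stands. The primary outcome, the power and the randomised comparison are unaffected. A reader might also take the baseline exclusion as the protocol's own judgement of risk, but the reason it gives is regulatory: "South Africa has not yet approved PrEP initiation during pregnancy".
- **Month 24 is not a settled cut-off.** This stands. A reader might infer that all late conceptions go unrecorded. The documents do not support that: the Trial status date would cover them, and even under a month-24 stop, losses and preterm births before the last visit among women who continue would be recorded.
- **Recording everyone would not give a fair comparison.** This stands. Women choose whether to stop, so stopped and continued groups are self-selected. Fuller recording describes all exposed pregnancies, but it does not make the contrast between the groups causal.

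**Conclusion.** The point holds in a limited form. Pregnancy testing provides for recording pregnancy and birth outcomes only for women who continue PrEP, a choice that can follow up to about 3 months of exposure. A birth-outcome summary made under that rule would be selective, and neither adverse-event collection nor pregnancy counts would complete it.

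The size cannot be stated as a number of women. A reader might infer that most exposed pregnancies in women who stop would have no recorded outcome, but the article gives no pregnancy rate, no stopping rate and no rate of capture through adverse events.

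The follow-up question is a conflict to reconcile, not a demonstrated loss. If month 24 is the end, roughly 36 to 37.5% of conceptions would reach term after the last visit, assuming uniform conception over 24 months, no attrition and about 266 days to 9 months to term. If November 2022 governs, the calendar covers all of them.

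This is a worthwhile, inexpensive improvement to safety data. It does not threaten the trial's main result.

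**What to change.** - **Pregnancy testing:** reword the recording rule to cover every participant with a positive pregnancy test after enrolment, whether or not she continues PrEP. Record the estimated conception date, the last PrEP pick-up, and the pregnancy and birth outcome.
- **Reporting:** give these outcomes to the DSMB descriptively, split by stopped or continued, and state that the split is self-selected and not an unbiased comparison.
- **End of follow-up:** reconcile the 2-year individual follow-up (data collection section, ethical considerations, Table 2) with the November 2022 date in Trial status. State that pregnancies ongoing at month 24 are followed to outcome by phone or record contact within that window.

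The woman's choice about PrEP stays as it is.

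**Cost:** a wording change, one outcome form, and a small amount of data collection after month 24. Staff already contact participants each month by SMS and phone, so the extra contacts are modest. The change would go to the ethics committee, as the article requires for any modification, and consent should be checked to see that it covers contact after month 24.

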#### Creatinine testing

Creatinine clearance will be assessed to monitor kidney function at baseline, month 3, month 12, and month 24. Clinical assessment for PrEP continuation will occur if estimated glomerular filtration (eGRF) rate is less than 60 mL/min. If eGRF does not improve, the participant will be terminated from the study due to risk of kidney damage and will be provided a referral letters for renal management and care.

#### Tenofovir testing

To assess PrEP adherence, tenofovir-diphosphate levels will be assessed at months 3, 6, 12, 18, and 24. Dried blood spots (DBS) will be prepared from venous blood and spotted on Whatman protein saver cards. Drug concentration testing will occur at the University of Cape Town Division of Pharmacology laboratory using DBS TDF testing protocols [60].

### Sample size and power calculations

A sample size was calculated to have 80% power to detect differences in the proportion of participants adhering to PrEP among the three study arms (Aim 2) using the chi-square test for independence with two degrees of freedom, with an alpha of 0.05, and assuming an attrition rate of 10% for those who (1) withdraw voluntarily from the study, (2) initiate on PrEP but withdraw due to adverse events (e.g. hepatic or renal abnormalities), or (3) become ineligible for PrEP (e.g. seroconvert). The effect size estimate was informed by prior experience from the field, where an effect size of 0.30 has been found between ART clients receiving some adherence support and those receiving none. However, we use a more conservative effect size of 0.15, to account for the fact that adherence support may not lead to the same gains in adherence among HIV-negative PrEP clients as it does with HIV-positive ART clients. The sample size was calculated to be 160 per arm (480 total).

### Primary and secondary outcomes

For Aim 1, our primary outcome will be the proportion of eligible individuals accepting PrEP as part of CBCT services. Secondary outcomes will include (1) stratification of PrEP initiation by both location and CBCT platform; (2) in-depth qualitative understanding of PrEP initiation; (3) correlates of immediate, delayed, and no PrEP initiation; and (4) comparison of sexual behaviours, risk profiles, and self-perception of risk in immediate, delayed, and never acceptors. Using the IMB model to inform the selection of variables and contextualization of results, an assessment of determinants of PrEP uptake will include (1) socio-demographic factors, (2) risk behaviours, (3) self-perception of risk, (4) previous knowledge of PrEP and perception of those taking PrEP, (5) partner characteristics and HIV status, (6) HIV-related stigma, and (7) screening scores for depression, substance abuse, and social support. Baseline STIs will be used as an independent marker of sexual risk behaviour, and to validate self-reported sexual risk behaviours and self-perception of risk.

For Aim 2, the primary outcome will be a comparison of TFV-DP levels by study arm at months 3, 6, 12, 18, and 24, with a 12-month primary outcome and 24-month assessment of intervention durability. Based on cumulative adherence behaviour, as measured in iPrEX OLE [14], adherence will be categorized as (1) *low adherence* (≤ 3 tablets per week; ≤ 699 fmol/DBS punch), and (2) *high adherence* (4–7 tablets per week; ≥ 700 fmol/DBS punch). Analysis of primary outcomes will be conducted on an intention-to-treat basis. Secondary outcomes will include (1) predictors of PrEP adherence after adjusting for study arm, socio-demographic factors, exposure to adherence support activities, and risk profiles; (2) characterization of changes in sexual behaviours and risk profiles following PrEP initiation; (3) proportion of individuals who discontinue PrEP and factors associated with discontinuation; (4) proportion of individuals who discontinue but subsequently restart PrEP and characteristics associated with this subgroup; (5) factors associated with of patterns of PrEP use; and (6) profiles of individuals that may benefit more from group-based vs. individualized adherence support.

For Aim 3, we will estimate incremental costs relative to standard practice for the intervention. Micro-costing studies will use activity-based approaches for costs incurred (e.g. start-up activities, recruitment, service delivery, lab monitoring, adherence support, and PrEP) and costs averted (e.g. health costs saved by averting HIV infections). Adjusting for time spent on research activities (e.g. informed consent, research questionnaires), the total time required for the intervention will be estimated. Time and costs for PrEP delivery through community-based platforms will be estimated through staff interviews, accounting for time available for the intervention. Costs incurred by patients to access PrEP will be assessed through participant interviews. Furthermore, we will estimate the impact of PrEP strategies by measuring: (1) the difference in HIV incident cases among intervention and control arm participants, (2) changes in HIV incident cases at the population level, and (3) changes in disability-adjusted life years (DALYs) between intervention and control arm participants. The model simulates intervention impact and projects the effect on health outcomes over 10 years. Sensitivity analyses will explore the impact of PrEP uptake and adherence on model outcomes outside a study setting, reduction in HIV transmission due to ART adherence, and PrEP supply-chain interruptions.

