## Study rationale and aims

Few studies have explored effective strategies to identify and deliver non-clinic-based PrEP services to at-risk populations, how to support prevention-effective use and retention in PrEP care, or implementation science approaches to scaling up PrEP delivery. Given that CBCT platforms have been shown to be highly acceptable and accessible to adolescent girls and young women, it is crucial to understand if these platforms can also be used to identify and deliver PrEP to at-risk youth [14–16]. Furthermore, community-based prevention-effective PrEP adherence support is critical to reduce the HIV burden among AGYW in South Africa. Towards this, our study aims include (Table 1):
Aim 1: PrEP service delivery: To determine the acceptability and feasibility of PrEP uptake by AGYW when delivered through community-based HIV counselling and testing platforms;Aim 2: PrEP adherence support: To evaluate community-based, scalable interventions to achieve prevention-effective adherence to PrEP among AGYW; andAim 3: Scalability of community-based PrEP services: estimate the cost per AGYW initiated on PrEP and provided adherence support through community-based platforms, and the cost per incident HIV infection averted.

**Table 1 Tab1:** Study overview: aims, rational, hypothesis, design and outcomes

	Hypothesis	Rational	Study design and approach	Primary outcome	Secondary outcomes
**Aim 1**	CBCT platforms will facilitate access to and initiation of PrEP by adolescent girls and young women	Numerous barriers exist that delay or inhibit YW’s access to clinic-based reproductive health and HIV prevention services	Cross-sectional, mixed methods. Integrate PrEP initiation services into CBCT pop-up testing sites and home-based testing platforms in extremely high HIV burden and under-researched rural and urban settings of South Africa	The proportion of eligible young women accepting PrEP as part of CBCT services	(1) PrEP initiation rates by a) community type (urban vs. rural), and b) CBCT platform (*pop-up testing sites vs systematic home-based testing*); (2) In-depth qualitative understanding of immediate, delayed and never accepting PrEP; (3) Socio-demographic and behavioural correlates of immediate, delayed and never initiating PrEP

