**Aim 2**	Cognitive behavioural-based adherence support programmes will be associated with a substantial increase in prevention-effective use of PrEP compared to a control	Lack of PrEP efficacy in African YW in clinical trials was strongly associated with poor adherence. To maximize the prevention benefits of PrEP, scalable adherence support interventions are needed	Randomized controlled trial. Enrol and randomize *PrEP-accepting young women* to receive one of two adherence support interventions or standard care (basic adherence support)	Comparison of tenofovir-diphosphate concentration levels in dried blood spots by study arm, with a 12-month primary outcome and 24-month assessment of intervention durability	(1) Predictors of PrEP adherence after adjusting for study arm, socio-demographic factors, exposure to adherence support activities, and risk profiles; (2) Characterization of changes in sexual behaviours and risk profiles following PrEP initiation; (3) Proportion of individuals that discontinue PrEP and factors associated with discontinuation; and (4) Qualitative description and factors associated with of patterns of PrEP use
**Aim 3**	Community-based PrEP initiation and adherence support platforms will increase uptake of and adherence to PrEP among YW, and cost-effectively avert HIV infections compared to standard practice	Evidence on cost and cost-effectiveness can be used by decision makers regarding the use of resources to support PrEP scale-up	Mathematical modelling and micro-costing studies. Estimate incremental costs and cost-effectiveness of community-based PrEP initiation and adherence support programmes among YW relative to standard practice.	Estimate the cost-effectiveness and budget impact of targeted PrEP initiation and adherence support	(1) Micro-costing studies will evaluate costs incurred and costs averted; (2) Estimate impact of support interventions on HIV incidence, HIV-related deaths and DALYs, using proportion on PrEP

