## Methods

### Study design and flow

The Community PrEP Study will enrol a cohort of 480 HIV-negative South African AGYW aged 16–25 years, incorporating multiple study designs to address our three main study aims (Table 1). Specifically, a cross-sectional, mixed-methods study design will be used to quantitatively measure and qualitatively assess the acceptability and feasibility of using CBCT platforms to identify HIV-uninfected AGYW and offer PrEP (Aim 1). A randomized controlled trial will evaluate a behavioural intervention aimed at supporting prevention-effective adherence to PrEP (Aim 2). Finally, we will perform micro-costing and mathematical modelling analyses to calculate the cost-effectiveness of our PrEP delivery platform and adherence support programmes (Aim 3). Community advisory boards (CABs) were established to facilitate community engagement and acceptance, elicit feedback on study design, conduct analysis, and ensure that community views and perspectives were appropriately incorporated in a collaborative manner.

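### The only horizon stated for the Aim 3 model is 10 years for health outcomes; for women aged 16–25 this would leave a substantial share of averted deaths and DALYs uncounted and make cost per DALY averted look worse than it is

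*Protocol article*

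**What the plan says.** The Aim 3 paragraph of Primary and secondary outcomes states the horizon: "The model simulates intervention impact and projects the effect on health outcomes over 10 years". No other horizon is given.

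The health outcomes are named in two places. The same paragraph lists "changes in disability-adjusted life years (DALYs) between intervention and control arm participants", and Table 1 (Aim 3, secondary outcomes) has "Estimate impact of support interventions on HIV incidence, HIV-related deaths and DALYs, using proportion on PrEP". Savings enter through micro-costing, as "costs averted (e.g. health costs saved by averting HIV infections"; no time limit is attached to them there.

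The Aim 3 primary outcome in Table 1 combines two questions: "Estimate the cost-effectiveness and budget impact of targeted PrEP initiation and adherence support". The aims list under Study rationale and aims adds "the cost per incident HIV infection averted". Under Study design and flow the cohort is "480 HIV-negative South African AGYW aged 16–25 years".

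The planned sensitivity analyses begin: "Sensitivity analyses will explore the impact of PrEP uptake and adherence on model outcomes outside a study setting". The remaining two concern the effect of ART on transmission and interruptions in PrEP supply.

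**The concern.** After 10 years a woman who entered at 16–25 is 26–35. If she avoided infection early in the programme, most of the life-years at stake may still lie ahead of her. The cost of preventing the infection is incurred no later than the infection would have occurred, while deaths and disability averted come afterwards. Cutting health outcomes at a fixed calendar point therefore removes benefit without removing the matching prevention cost.

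Ten years is a reasonable period for budget impact. It fits cost per DALY averted poorly, yet it is the only horizon stated for both. Aim 3 hypothesises that the programme averts infections cost-effectively, and the Discussion offers the result to policy makers. A truncated ratio leans against that hypothesis, and the planned sensitivity analyses would not reveal it.

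**Working it through.** The 10 years is a design choice, so there is no figure in the plan to reproduce. The question is what share of the lifetime benefit of one averted infection falls before year 10.

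**Inputs from the article.** Horizon 10 years; age 16–25; outcomes include deaths, DALYs and averted care costs.

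**Assumed inputs, none of them in the article.** Constant excess mortality m after infection of 1% or 2% a year (5% and 8% as stress cases); T = 45 remaining years without infection (25 as a stress case); infection averted at a time u spread evenly over years 0–2 (or 0–10); ART starting 0 or 2 years after infection (5 in the full grid); discount rate r of 0, 3% or 5%; disability weight 0.078 while living with HIV.

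**Deaths (undiscounted).** Share inside = (1 − e^(−m(10−u))) / (1 − e^(−mT)). At the midpoint u = 1, T = 45:
- m = 1%: 0.0861 / 0.3624 = 0.24
- m = 2%: 0.1647 / 0.5934 = 0.28

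So 72–76% of averted deaths fall after year 10.

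**DALYs.** Let s be years since infection and S(s) = e^(−ms). Two counting rules give the same lifetime total but place it differently in time.
- *Year by year as lost:* integrate 0.078·S + (1 − S). For m = 2%, r = 0, u = 1, the first 9 years after infection hold 1.406 of a lifetime 17.643, a share of 0.08. Over m = 1–2% and r = 0–5% the share is 8–24%, so 76–92% falls outside.
- *All remaining life-years attached at the date of death:* integrate 0.078·S + m·S·(T − s). For m = 1%, r = 0, u = 1: 4.163 / 11.589 = 0.36. Over the same ranges the share is 36–54%, so 46–64% falls outside.

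**Effect on cost per DALY averted.** With the numerator held fixed, the ratio is multiplied by 1/share: about 1/0.54 = 1.9 to 1/0.36 = 2.8 with life-years attached at death, and 1/0.24 = 4.2 to 1/0.08 = 12.5 counted year by year.

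**Averted ART cost, only if it too stops at year 10.** Share inside = ∫e^(−(m+r)s)ds from ART start to 10 − u, divided by the same integral to T. At u = 1 the lowest case (m = 1%, r = 0, start at 2 years) is 6.627 / 34.257 = 0.19 and the highest (m = 2%, r = 5%, immediate start) is 6.677 / 13.674 = 0.49. So 51–81% would be lost.

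**Where the loss is smaller.** Share inside 10 years, infections averted in years 0–2:

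| Case | ART cost | Deaths | DALYs, at death | DALYs, year by year |
|---|---|---|---|---|
| m = 1–2%, T = 45 | 19–49% | 24–28% | 36–54% | 8–24% |
| m = 8%, T = 45 | 44–69% | 53% | 64–72% | 9–22% |
| T = 25, maximum over the grid | 72% | 59% | 80% | 36% |

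**Where it is larger.** If averted infections are spread over all 10 years with T = 45, no share inside exceeds 50% anywhere in the grid: ART cost 4–47%, deaths 13–32%, DALYs 4–14% (year by year) or 21–50% (at death).

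**Opposite effect.** Some infections are delayed, not averted. Using the incidences under Study location (0.74% adults, 2.40% female youth) as constant future rates, a further 10 years gives 1 − e^(−0.074) = 7% to 1 − e^(−0.24) = 21% later infected. This is smaller than the truncation in most scenarios.

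**The case against.** The strongest reply is that one compressed sentence in an article is not a model specification. Four parts of it stand.

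- **Costs.** The 10 years is attached to health outcomes. A reader might infer that averted treatment cost also stops there, but the text does not say so: a lifetime treatment cost could be attached to each infection averted within the horizon. The 51–81% for ART cost is therefore conditional. If costs are in fact lifetime, costs and DALYs in one ratio would run over different periods, which would also need correcting.
- **Programme period.** A reader might infer that all programme cost falls in the first two years. Two years is the trial's follow-up; the article does not say how long the modelled programme runs, and its references to scale-up and supply interruptions fit continuing delivery. Continuing delivery does not remove the truncation; it leaves less time inside the horizon for later averted infections.
- **'Most'.** It is tempting to say that most of the benefit is always lost. The article does not supply the inputs for that, and it fails in part of the range above, chiefly for DALYs attached at death and under high mortality.
- **Scope.** Cost per infection averted rests on a count and barely depends on the later years, apart from the delayed infections, and budget impact is by nature a finite-horizon result.

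The discount rate and DALY counting rule may well be in a fuller modelling plan, and their absence here is not a criticism. The horizon differs because the article states it.

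**Conclusion.** The point holds for cost per DALY averted. Followed as written, a 10-year limit on health outcomes in women aged 16–25 drops late benefit and biases that ratio against the programme. Under the assumed 1–2% excess mortality, 45 remaining years and early averted infections, about 72–76% of averted deaths and 46–92% of averted DALYs are lost. Higher mortality or a shorter life span reduces this, and delayed infections offset a further part.

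For net cost the point is conditional on the cut also applying to averted treatment cost. The documents do not support a claim that Aim 3 as a whole is biased, nor a single multiplier for the understatement. The randomised comparison in Aim 2 is untouched. The change is worth making because it bears on part of Aim 3's primary outcome and no planned sensitivity analysis would show the effect.

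**What to change.** Report cost per DALY averted and net cost over a discounted lifetime horizon of the simulated women alongside the 10-year horizon. Within each ratio, use the same horizon for costs and for health outcomes, and state whether life-years after year 10 are counted for deaths that occur before it. Keep 10 years for budget impact.

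This needs longer model runs and an extra column of results, but no new trial data. The drawback is more extrapolation in survival, treatment cost and later infection risk. For that reason both horizons should be shown; making lifetime the sole base case would be more debatable.
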